### Quality assurance system

The steering committee, composed of principal investigators (PI) from each sub-center, is responsible for monitoring the progress of the trial, training researchers before the study begins, reviewing adverse events, and developing statistical analysis programs with a statistician. Each sub-center has a clinical research assistant (CRA), and the five of them form the data monitoring committee. CRAs are responsible for checking all documents, such as case report forms (CRFs), related to this trial and coordinating all aspects of local organization. Each committee meets annually to review the trial process, and the interim analysis will take place in the second year of the study; the five research units will share the analysis results. Monitoring will be conducted independently from the PI and sponsors.

If the protocol is to be revised, it must be approved by the IRB of each research center, and the project lead unit may terminate all studies early due to medical reasons. In addition, if the research cannot be carried out in accordance with the research protocol agreement or if any other reason is found, the project lead unit has the right to terminate the research at any time. If the research is terminated or suspended early, the project lead unit should immediately notify the CRO, medical institution, management department, and IRB of the branch center of the decision and its reasons. All research materials must be returned to the project lead unit.

### Safety monitoring

#### Adverse events

Adverse events (AEs) are defined as any symptoms, syndromes, or diseases that affect the patient’s health during the observation period of this clinical study and also involve clinically relevant events found in the laboratory or other diagnostic processes. Examples include the need for unplanned treatment measures which result in patients withdrawing from the study, or when clinically meaningful laboratory test items are abnormal. Serious adverse events (SAEs) consist of (1) death, (2) life-threatening events, (3) hospitalization, (4) permanent or severe disability after fire needle therapy, (5) events leading to congenital malformations after fire needle treatment, and (6) the need for medical treatment to prevent permanent injury or damage. Fire needle therapy is considered safe, and no obvious AEs or SAEs have been reported in clinical application.

#### Management of AEs and SAEs

Researchers should always carefully observe the patient’s skin lesions and systemic performance during fire needle treatment. If any AEs occur during treatment, the researcher should complete the “adverse event form” within the CRF and conduct a follow-up investigation; they should record the treatment process in detail until the laboratory test is normal and the symptoms and signs disappear. In addition, once AEs occur, the researcher should make a diagnosis, initiate treatment according to the condition, and decide whether to stop the clinical observation. In the event of SAEs, the unit undertaking the clinical research must immediately take the necessary measures to protect the safety of the participants. The researcher will then complete the “Serious Adverse Event Report Form” within the CRF. He or she will report to the subject responsible unit as well as the ethics committee of the unit within 24 h and sign and date the report. The research responsible unit will report the SAEs to the participating units in a timely manner and ensure that the reporting procedures meet all laws and regulations. Once the steering committee determines whether the AEs or SAEs are related to this study, the research team will provide treatment costs and financial compensation for trial-related damages.

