Exclusion criteria will be applied as follows: (1) presence of other progressive skin diseases that may affect assessment of the condition; (2) treatment with the research drugs, biological agents, and immunosuppressive agents within 1 month before study initiation; (3) treatment with topical glucocorticoids and/or phototherapy within 2 weeks before study initiation; (4) presence of severe, uncontrolled, local or systemic, acute or chronic infection; (5) presence of severe systemic diseases, elevation of alanine aminotransferase or aspartate aminotransferase levels by > 1.5 times the upper limit of normal, elevation of creatinine by 1.5 times the upper limit of normal, decrease in any main blood test parameters (white blood cell count, red blood cell count, hemoglobin amount, platelet count) to below the lower limit of normal, or abnormalities in other laboratory test parameters; (6) history of malignant neoplasms, primary or secondary immune deficiency, and/or a hypersensitivity reaction; (7) major surgery within 8 weeks before study initiation or scheduled during the study period; (8) pregnancy or lactation; (9) history of alcohol abuse or drug abuse, family history of cancer, personal or family history of a serious mental illness; (10) any other factors considered by the researchers as contraindications for study participation.

Criteria for trial suspension, patient rejection, and patient withdrawal are also set as follows: (1) development of other serious or life-threatening organic lesions during the trial, (2) withdrawal at the individual’s discretion, (3) poor patient adherence to treatment, (4) participation in another trial administering treatment that may interfere with the results of the present study, (5) refusal to take contraceptive measures during the trial period (including both treatment and follow-up periods), (6) loss to follow-up for various reasons, and (7) incorrect application of the inclusion and exclusion criteria.

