#### Safety

Safety assessments will include vital sign monitoring, routine blood tests, blood biochemistry, routine urine tests, pregnancy tests, physical examinations, and the recording of adverse events (including serious adverse events). Participants will be monitored for their vital signs, adverse events, and serious adverse events throughout the research period. Routine blood and urine tests and blood biochemistry will be conducted at the time of screening and during the 4th week of treatment. Pregnancy tests will be conducted only at the time of screening. Physical examinations will be conducted at the time of screening, during the 4th week of treatment, and throughout the follow-up period (Table 2).

**Table 2 Tab2:** Timeline for a randomized trial evaluating fire needle therapy for blood stasis syndrome of plaque psoriasis

	Research cycle	Screening period	Baseline period	Treatment period				Early termination	Follow-up period	
	Time point	Week 1	Week 0	Week 1	Week 2	Week 3	Week 4		Week 6	Week 8
**Enrollment**	**Inclusion/exclusion criteria**	**●**	**●**							
	**Informed consent**	**●**								
	**Demographic characteristics**	**●**								
	**Medical history**	**●**								
	**Registration**	**●**								
	**Randomization**		**●**							
	**Photographs of skin lesions**		**●**	**●**	**●**	**●**	**●**	**●**	**●**	**●**
**Interventions**	**Basic therapy + fire needle therapy**		**★-------------------------------------------------------------------★**							
	**Basic therapy + fire needle control therapy**		**☆-------------------------------------------------------------------☆**							
**Assessment**	**PASI**	**●**	**●**	**●**	**●**	**●**	**●**	**●**	**●**	**●**
	**BSA**	**●**	**●**	**●**	**●**	**●**	**●**	**●**	**●**	**●**
	**PGA**	**●**	**●**	**●**	**●**	**●**	**●**	**●**	**●**	**●**
	**DLQI**		**●**	**●**	**●**	**●**	**●**	**●**		
	**PRQoL**		**●**	**●**	**●**	**●**	**●**	**●**		
	**VAS**		**●**	**●**	**●**	**●**	**●**	**●**	**●**	**●**
	**TCM symptom**		**●**	**●**	**●**	**●**	**●**	**●**		
	**Recurrence rate**								**●**	**●**
**Safety**	**Vital signs**	**●**	**●**	**●**	**●**	**●**	**●**	**●**	**●**	**●**
	**Blood routine**	**●**					**●**	**●**		
	**Blood biochemistry**	**●**					**●**	**●**		
	**Urine routine**	**●**					**●**	**●**		
	**Concomitant medication**	**●**	**●**	**●**	**●**	**●**	**●**	**●**		
	**Pregnancy test**	**●**								
	**Physical examination**	**●**					**●**	**●**	**●**	**●**

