### Statistical analysis

A statistician will formulate a plan for statistical analysis in consultation with the PI. All analyses will be conducted using SAS statistical software, and the data network platform will be designed by the data management center of Nanjing Ningqi Medical Technology Co., Ltd., which will be entrusted with the third-party statistical analyses. The measurers will be blinded to the results. The overall principles will be as follows: An intention-to-treat (ITT) and per-protocol analysis will be used for statistical analysis. Quantitative variables (such as PASI, BSA, PGA, DLQI, PRQoL, VAS, and TCM syndrome scores) will be expressed as mean and standard deviation values or as median values with lower (Q1) and upper (Q3) quartiles. If the quantitative variables conform to normal distribution, a *t* test will be used (The homogeneity test will be performed for the two groups, with 0.05 as the significance level. The Satterthwaite method will be used to correct the *t* test when the variance is not uniform). If quantitative variables conform to skewed distribution, a nonparametric test will be used. Qualitative variables (such as cure rate, recurrence rate) will be expressed as numbers and percentages or composition ratios. Statistical inference will be performed using chi-square tests, Fisher’s exact tests, and Wilcoxon rank sum tests, among others. Potential confounding factors affecting the main outcome indicators will be adjusted by logistic regression. In this study, a *p* value of less than 0.05 is considered as statistically significant.

To account for missing data, we considered participants who may not complete the follow-up when calculating the sample size. The reasons, main characteristics, and data of a patient’s failure to follow-up will be recorded. Other types of randomly missing data will be considered unsuccessful according to the principle of ITT analysis.

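### After an adverse event the protocol speaks of stopping observation, not treatment; its sections on this disagree, and later PASI and safety visits may be lost

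*Protocol article*

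**What the plan says.** Five places in the protocol article bear on this point.

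- **Management of AEs and SAEs**, on what may be stopped once any AE occurs: "the researcher should make a diagnosis, initiate treatment according to the condition, and decide whether to stop the clinical observation". There is no severity threshold, and the thing stopped is observation. Stopping the needling is not mentioned separately.
- **Same section**, on the follow-up duty: "they should record the treatment process in detail until the laboratory test is normal and the symptoms and signs disappear".
- **Inclusion and exclusion criteria**, last paragraph: "Criteria for trial suspension, patient rejection, and patient withdrawal are also set as follows". One list serves all three purposes. Its only health-event item is "development of other serious or life-threatening organic lesions during the trial". It has no item for an ordinary AE or for the researcher's judgement.
- **Adverse events**: one example of an AE is "the need for unplanned treatment measures which result in patients withdrawing from the study", so AE-related withdrawal is foreseen here.
- **Safety, Table 2**: an "Early termination" column marks PASI, the other scales, laboratory tests, physical examination, AEs and SAEs.

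For the analysis, the Statistical analysis section states: "An intention-to-treat (ITT) and per-protocol analysis will be used for statistical analysis". It then says that possible non-completion was considered in the sample size, that reasons for failed follow-up will be recorded, and that other data missing at random count as unsuccessful.

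**The concern.** A decision to stop treatment and a decision to stop collecting data are different, and an intention-to-treat analysis depends on keeping them apart. Here they are merged, and the grounds for the decision differ between sections. One site could keep a patient with a non-serious AE because the withdrawal list does not name it. Another could end that patient's participation under the AE section.

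Patients stopped for an AE are unlikely to be a random subset, so the data lost are probably informative. The arms differ in whether the needle is heated, so losses could also differ by arm. Both stated aims are exposed: efficacy, through PASI after the stop, and safety, through the later scheduled checks. An analysis plan can choose how to handle missing values, but it cannot recover visits that sites were told they could end.

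**Working it through.** **1. The sections side by side.** The AE management section allows a stop after any AE. The AE definition agrees that AEs may lead to withdrawal. The withdrawal list has no matching ground short of serious or life-threatening organic lesions. It is not said to be exhaustive, so this is an inconsistency and not two rules that exclude each other.

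**2. What a stopped patient may lose, from Table 2.** Scheduled post-baseline PASI ratings are at Weeks 1, 2, 3, 4, 6 and 8, six in all.

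- Stop after Week 1: Weeks 2, 3, 4, 6 and 8 may be lost (5 of 6).
- Stop after Week 3: Weeks 4, 6 and 8 may be lost (3 of 6).
- Stop after Week 4: Weeks 6 and 8 may be lost (2 of 6).

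One Early termination assessment replaces them. Vital signs, physical examination, AEs and SAEs are also scheduled at Weeks 6 and 8. Laboratory tests are scheduled only to Week 4 and are repeated at early termination.

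**3. Whether the missing-data rule covers these patients.** The rule is worded for data missing at random, which an AE-driven stop is not clearly. It also yields a success or failure, while the primary outcome is a decrease in PASI, for which a t test or nonparametric test is planned. Coverage is unclear on both counts.

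**4. Size, by illustration.** Inputs from the Sample size section: p1 = 0.768, p0 = 0.353, two-sided alpha 0.05, power 0.90.

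The plan's own figure first: n = [0.768 × 0.232 + 0.353 × 0.647] / 0.415² × (1.960 + 1.282)² = 24.80, so 25 per group, as stated. The plan then moves to 38 and, with dropout, to 47 per group.

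The documents give no AE or stopping rate. Assume that a share s of the fire needle arm is stopped for an AE and none of the control arm.

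- *Handling A, counted as unsuccessful, with stops independent of response:* difference = 0.768 × (1 − s) − 0.353. Power uses the normal approximation with pooled variance under the null.
- *Handling B, dropped, with every stopped patient a would-be failure (an extreme case):* difference = 0.768 / (1 − s) − 0.353.

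| s | A: difference | A: power, 47 per group | A: power, 38 per group | B: difference |
|---|---|---|---|---|
| 0 | 41.5 points | 98.9% | 96.8% | 41.5 points |
| 5% | 37.7 | 96.7% | 92.5% | 45.5 |
| 10% | 33.8 | 92.0% | 85.4% | 50.0 |
| 20% | 26.1 | 72.5% | 63.0% | 60.7 |

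The two handlings move the result in opposite directions. Each is neutral under the other's assumption: counting would-be failures as failures leaves 76.8%, and so does dropping patients whose stop is unrelated to response.

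On the PASI scale, if patients are dropped, the shift in the arm mean is s times the shortfall in PASI decrease among those stopped. With assumed s of 5% to 15% and an assumed shortfall of 1 to 2 points, this is 0.05 × 1 = 0.05 to 0.15 × 2 = 0.30 PASI points. For an arm of 47, that is 0.05 × 47 = 2.4 to 0.15 × 47 = 7.1 patients.

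**The case against.** The case against is substantial, and it limits how far the point can go.

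- *A reader might infer that the AE section contradicts the withdrawal list.* The list does not claim to be complete and does not forbid AE-related exit, and the AE definition expects it. The sections are inconsistent, no more.
- *A reader might infer that stopping observation contradicts the duty to follow AEs.* The duty comes first and is unconditional, and an AE can be followed to resolution after scheduled trial visits end. The wording is ambiguous, but the two can be reconciled.
- *A reader might infer that efficacy data are removed outright.* Table 2 keeps a PASI at early termination, and no text says that such a patient must skip Weeks 6 and 8. Only later visits are at risk.
- *A reader might infer that losses fall mainly on the fire needle arm and flatter it.* Heating makes imbalance plausible, but the protocol gives no rates, states that no obvious AEs have been reported with fire needling, and tells patients in both arms that mild local reactions are normal. Under the counted-as-unsuccessful rule, excess stops would work against fire needling.
- *A reader might infer that the decision lies with someone who knows the allocation.* The deciding researcher is not identified as the operator, and the masking section says that all staff except the recruiting observer are blinded. Whether that is achievable is a separate question.

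It can also be said that the unseen analysis plan may settle how such patients are analysed. That is fair for analysis but not for collection. What stands is the inconsistency between sections, the merging of treatment with assessment, and the resulting risk to later visits.

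**Conclusion.** The point holds as an inconsistency in stated text with an avoidable risk of informative missing data. The three sections give different grounds for ending a patient's participation after an AE, and none distinguishes stopping treatment from ending assessments. Read as written, up to five of six post-baseline PASI ratings and the Week 6 and 8 safety checks may be lost for a stopped patient.

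The effect on the treatment comparison cannot be computed from the documents. The shifts shown rest on an assumed excess stopping share, on no stops in the control arm, and on assumptions about who is stopped and how they are analysed. With equal stopping in both arms, the imbalance would not arise. No direction of bias is established. This is a cheap improvement.

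**What to change.** 1. Reconcile the withdrawal list, the AE definition and the AE management section so that they give the same grounds. Which clinical grounds apply is for the investigators.
2. State separately what it means to stop study treatment and what it means to end study assessments.
3. State that a patient whose treatment is stopped for an AE continues, with consent, the remaining scheduled assessments in Table 2 through Week 8, with PASI rated by the blinded measurer and the data included in the intention-to-treat analysis.
4. Reserve the Early termination visit for patients who decline further visits.

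The cost is a protocol revision, which the Quality assurance system section says each centre's review board must approve, and a few more visits by patients no longer treated. The visits themselves are already scheduled.

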### Data confidentiality and management

With the exception of the CRO responsible for the participants, participants’ information will be kept confidential from research staff until publication of the study results. All of their documents related to this trial, such as CRFs, will be represented by the participant’s unique random code. Random codes and CRFs will be sealed and stored in a separate filing cabinet. To facilitate data analysis, CRO will also use a unified data collection system for recording (established by Nanjing Ningqi Medical Technology Co., Ltd. Data Management Center, Nanjing, China). The results of this trial will be published in an international peer-reviewed journal.

### Statistical analysis

A statistician will formulate a plan for statistical analysis in consultation with the PI. All analyses will be conducted using SAS statistical software, and the data network platform will be designed by the data management center of Nanjing Ningqi Medical Technology Co., Ltd., which will be entrusted with the third-party statistical analyses. The measurers will be blinded to the results. The overall principles will be as follows: An intention-to-treat (ITT) and per-protocol analysis will be used for statistical analysis. Quantitative variables (such as PASI, BSA, PGA, DLQI, PRQoL, VAS, and TCM syndrome scores) will be expressed as mean and standard deviation values or as median values with lower (Q1) and upper (Q3) quartiles. If the quantitative variables conform to normal distribution, a *t* test will be used (The homogeneity test will be performed for the two groups, with 0.05 as the significance level. The Satterthwaite method will be used to correct the *t* test when the variance is not uniform). If quantitative variables conform to skewed distribution, a nonparametric test will be used. Qualitative variables (such as cure rate, recurrence rate) will be expressed as numbers and percentages or composition ratios. Statistical inference will be performed using chi-square tests, Fisher’s exact tests, and Wilcoxon rank sum tests, among others. Potential confounding factors affecting the main outcome indicators will be adjusted by logistic regression. In this study, a *p* value of less than 0.05 is considered as statistically significant.

To account for missing data, we considered participants who may not complete the follow-up when calculating the sample size. The reasons, main characteristics, and data of a patient’s failure to follow-up will be recorded. Other types of randomly missing data will be considered unsuccessful according to the principle of ITT analysis.

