### Outcomes

#### Primary outcomes

The Psoriasis Area and Severity Index (PASI) is the gold standard assessment tool used to quantify the severity of psoriasis based on erythema, infiltration, scaling, and the extent of lesions [16]. As such, a decrease in the PASI score has been designated as the primary outcome of this study. This score will be evaluated at screening, at baseline, during the 4-week treatment period, and during the 4-week follow-up period. The researchers will use the PASI to assess the severity and area of lesions and simultaneously obtain photographs of typical skin lesions.

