### Sample size

In this study, the estimated post-treatment PASI score for all patients will be set at 50% lower than the pre-treatment score, both in the intervention group and the control group. The sample size of the current trial is calculated based on the following formula, and take the cure rate as the primary treatment effect index.
$$ n=\frac{p_1\times \left(1-{p}_1\right)+{p}_0\times \left(1-{p}_0\right)}{{\left({p}_1-{p}_0\right)}^2}{\left({z}_{\alpha /2}+{z}_{\beta}\right)}^2 $$

According to a previous study titled “Therapeutic Observation of Fire-needle Acupuncture for Stationary Plaque Psoriasis” [19], the cure rate to achieve this score is 76.8% for the intervention group and 35.3% for the control group. In this study, we set the inspection level (*α*) as 0.05, and the test power as 0.9, then *β* = 1–0.9 = 0.1. For two-sided tests, at least 25 participants would be required for each group. Considering the correlation of primary outcomes at different times and multicenter effect, we increase the sample size to 38 participants in each group, Considering a dropout rate of 20%, a total of 94 patients (47 per group) will be required for this study (Table 3).

**Table 3 Tab3:** Centers involved in a randomized trial evaluating fire needle therapy for blood stasis syndrome of plaque psoriasis

Research center	Sample size
Shaanxi Hospital of Traditional Chinese Medicine	20
Yueyang Hospital of Integrated Traditional Chinese and Western Medicine	20
First Affiliated Hospital of Heilongjiang University of Traditional Chinese Medicine	18
Affiliated Hospital of Jiangxi University of Traditional Chinese Medicine	18
Traditional Chinese Medicine Hospital of Shijiazhuang	18

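### PASI decrease has six post-baseline visits and none named primary; its stated tests are unadjusted, and the only stated adjustment, logistic regression, does not fit a continuous outcome.

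*Protocol article*

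**What the plan says.** **Outcome and timing.** Under Primary outcomes, "a decrease in the PASI score has been designated as the primary outcome of this study". On timing, the same section says: "This score will be evaluated at screening, at baseline, during the 4-week treatment period, and during the 4-week follow-up period". Table 2 (under Safety) marks PASI after baseline at Weeks 1, 2, 3, 4, 6 and 8, and at early termination. No visit is singled out as primary.

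**Sample size.** The Sample size section works from a different quantity, a binary cure rate of 76.8% against 35.3%, and obtains 25 per group. It then says: "Considering the correlation of primary outcomes at different times and multicenter effect, we increase the sample size to 38 participants in each group". No correlation or intraclass correlation is given for this step.

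**Analysis.** The Statistical analysis section lists PASI among the quantitative variables and gives two routes: "If the quantitative variables conform to normal distribution, a *t* test will be used", with a Satterthwaite correction if variances differ, and "If quantitative variables conform to skewed distribution, a nonparametric test will be used". Cure rate is listed among the qualitative variables. On covariates: "Potential confounding factors affecting the main outcome indicators will be adjusted by logistic regression". The threshold is p below 0.05, and no rule for several time points is given. The section announces a later plan by a statistician, but presents these items as its overall principles.

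**The concern.** The visit is part of the definition of a primary outcome. Here it is open, and the Sample size section treats more than one time as primary. Weeks 6 and 8 fall two and four weeks after the end of treatment, so they may answer a different question from Week 4. If the visit is chosen after the data are seen, the nominal 5% no longer describes the error rate.

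The stated adjustment also does not match the stated outcome. A logistic model needs a binary response. For a continuous PASI decrease, the plan as written therefore offers no adjusted analysis, and a five-centre trial is left with an unadjusted two-group comparison. Entry is limited by body surface area (at most 10%) and not by PASI. Baseline PASI may therefore vary between patients and be related to the size of the decrease, and an analysis without it as a covariate gives up precision.

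Finally, patients are added for the correlation over time and for centre, but nothing in the stated PASI analysis uses either feature.

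**Working it through.** **1. The plan's own figure.** Inputs from Sample size: p1 = 0.768, p0 = 0.353, two-sided α = 0.05, power 0.90.

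n = [p1(1−p1) + p0(1−p0)] / (p1−p0)² × (z₀.₉₇₅ + z₀.₉₀)²
= (0.1782 + 0.2284) / 0.1722 × 10.507 = 24.80, so 25 per group. This reproduces.

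The step to 38 is a factor of 38/25 = 1.52. It cannot be derived from anything stated. With 20% dropout, 38/0.8 = 47.5, against the stated 47.

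**2. Outcome, test and adjustment side by side.**

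| Item | PASI decrease | Cure rate |
|---|---|---|
| Type | continuous | binary |
| Named primary in | Primary outcomes | Sample size (as the effect index) |
| Stated test | t or rank test | chi-square or Fisher |
| Stated adjustment that can be fitted | none | logistic regression |
| Stated analysis using repeated times | none | none |
| Stated analysis using centre | none | only if chosen as a confounder |

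**3. Family-wise error, if any visit could count.** This is conditional on a rule that the documents do not state. There are six visits, each tested at two-sided 0.05.

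- Independent visits (upper reference): 1 − 0.95⁶ = 26.5%.
- Common correlation between visits (assumed; 400,000 simulated null vectors, largest of six correlated z statistics against 1.96):

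| Correlation | Family-wise error |
|---|---|
| 0.5 | 20.8% |
| 0.7 | 16.3% |
| 0.8 | 13.8% |
| 0.9 | 10.9% |

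- If correlation instead decays with the gap in weeks (AR(1), an alternative assumption), a weekly correlation of 0.7 gives 21.4% and 0.9 gives 14.7%.
- One pre-specified visit, or one pre-specified contrast: 5%.

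The documents give no between-visit correlation, so these are ranges and not estimates.

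**4. What a Bonferroni rule would need.** 0.05/6 = 0.0083 per visit. The plan's formula then gives 36.3, so 37 per group, and 37/0.8 = 46.25, so 47 with dropout. The planned size would carry that correction on the binary endpoint, but the plan states no such correction.

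**5. Baseline as a covariate.** Let r be the correlation of baseline with Week 4 PASI, with equal variance σ² at both times (both assumed).

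- Variance of the change score: 2σ²(1−r).
- Residual variance of ANCOVA: σ²(1−r²).
- Ratio: (1−r²) / [2(1−r)] = (1+r)/2.

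| r | Ratio | Variance cut | Extra patients the change-score test needs (1/ratio − 1) |
|---|---|---|---|
| 0.3 | 0.65 | 35% | 54% |
| 0.5 | 0.75 | 25% | 33% |
| 0.7 | 0.85 | 15% | 18% |

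If the two variances differ, the figures change. The direction does not: the change score is ANCOVA with its slope fixed at 1, so fitting the slope cannot raise the residual variance, apart from one degree of freedom.

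**The case against.** The strongest reply is that nothing says six primary tests will be run, or that one significant visit means success. The sentence on timing is a measurement schedule. Sample size compares post-treatment with pre-treatment PASI, so an end-of-treatment comparison is a natural reading. This stands: a reader might infer an any-visit rule, but the documents do not contain one, and the inflated error is therefore conditional.

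A reader might also infer that baseline PASI and centre play no part at all. That goes too far. A decrease uses baseline by definition, centre is named in the sample size, and the list of potential confounders is open. What remains is that neither is a covariate in any stated analysis of the continuous decrease.

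Nor is logistic regression wrong in itself. It suits the cure rate, and the sentence refers to outcome indicators in the plural. The fault lies in its being the only adjustment stated when the declared primary outcome is continuous.

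It is also fair that an unadjusted test in a randomised trial is valid, and that model details usually sit in an analysis plan. Lack of a mixed model, or use of a preliminary normality or variance check, is accordingly not counted as an error here. But the primary visit belongs in the protocol, and the article does not merely stay silent on method: it states unadjusted tests and a logistic adjustment as principles that a later plan would inherit.

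**Conclusion.** The point holds in this limited form. No primary PASI visit is fixed among six, while the sample size text treats several times as primary. The stated tests for PASI are unadjusted, the only stated adjustment cannot be applied to a continuous decrease, and the increase from 25 to 38 per group for time and centre has no matching PASI analysis.

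The size depends on assumptions. If any visit could be claimed, error would be about 14% to 21% at a common correlation of 0.5 to 0.8, and about 11% at 0.9, instead of 5%. Covariate adjustment would cut variance by 15% to 35% for r from 0.7 down to 0.3, under equal variances. The first is a risk that the text leaves open and not a rule it adopts. The second is a gain in precision and not a correction of bias.

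**What to change.** Before unblinding:

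1. Name one primary visit, for example Week 4 as the end of treatment, and make it the single two-sided 0.05 comparison. Label the other visits supportive.
2. Analyse PASI change at that visit by ANCOVA with arm, baseline PASI and centre. A repeated-measures model with the same covariates, reporting that visit's contrast, would serve equally well and would use the correlation over time that the sample size invokes.
3. Keep logistic regression, with baseline PASI and centre as covariates, for the binary cure rate only.
4. Reconcile Primary outcomes with Sample size on whether PASI decrease or cure rate is primary. If the continuous decrease stays primary, say what the calculation from 76.8% and 35.3% then supports.

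**Cost.** No new data are needed, and programming is slight. Other visits can no longer carry a primary claim. The Quality assurance system section requires approval by the review board of each centre for a protocol revision, so changing the outcome definition takes five approvals. Trial status dates the start of recruitment to June 2019 and its planned end to December 2020, so the change should be dated and shown to precede unblinding.
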